## Overview of research activities

An overview of the research activities, methods, and study instruments is provided in Table 1, with a discussion of each study component following. There are two broad research components: 1) an impact evaluation of the CR program and, 2) implementation sciences to provide insights to how the intervention was received among the target population and how to improve its effectiveness if it was to be scaled up in other settings.

**Table 1: Overview of research activities and methods**

| **Study Component** | **Impact Evaluation** | | **Implementation Science** | | |
| --- | --- | --- | --- | --- | --- |
| **Research Activity** | 1. **Stepped-wedge cluster randomized trial** | 1. **Extraction of routine program monitoring data** | 1. **In-depth interviews (IDIs) and focus group discussions (FGDs) with cohort participants** | 1. **IDIs and FGDs with Community Responses staff** | 1. **Observations of Stepping Stones Sessions** |
| **Study**  **population** | Panel of women (aged 18–24) and men (aged 18–35) living in selected communities | CCI monitoring data | Selected panel study participants:  women (ages 18–24) and men (ages 18–35) | Facilitators, staff, and program managers involved with Community Responses | Participants and facilitators in stepping stones sessions |
| **Sample size** | 1,500 participants:  750 women  750 men | Not applicable | 60 IDIs : 15 women, 15 men  6 FGDs: 2x 10 women  2x 10 men  2x 5 women/5 men | 10 IDIs : Program managers  4 FGDs: Program facilitators  and staff | Observation of approximately 5 – 10 sessions |
| **Location of**  **activity** | Ugu and eThekwini sub-districts, KwaZulu Natal, South Africa | Ugu and eThekwini sub-districts, KwaZulu Natal, South Africa | Ugu and eThekwini sub-districts, KwaZulu Natal, South Africa | Ugu and eThekwini sub-districts, KwaZulu Natal, South Africa | Ugu and eThekwini sub-districts, KwaZulu Natal, South Africa |
| **Timing** | Stepped-wedge intervention roll-out with 4 survey rounds (2016–2019):  *(See Table 2)* | Throughout follow-up period  (2016–2019) | After stepped-wedge intervention rollout (variable) and again at endline (Feb 2019) | After stepped-wedge intervention rollout (variable) and again at endline (Feb 2019) | During follow-up period  (2016–2019) |
| **Method** | Structured interviewer‐administered  interview | Record extraction | IDI & FGD | IDI & FGD | Unstructured observation |
| **Informed**  **Consent** | Adult (Annex A) | Not applicable: data aggregated at community level | Participant IDI (Annex B)  Participant FGD (Annex C) | Staff IDI (Annex D)  Staff FGD (Annex E) | Routine monitoring visits |
| **Study**  **Instrument** | Questionnaire  (Annex F) | Extraction tool | Participant IDI guide  (Annex G)  Participant FGD Guide (Annex H) | Staff IDI guide  (Annex I)  Staff FGD Guide (Annex J) | Observation notes |

## Impact evaluation

A **stepped-wedge cluster randomized trial** with an embedded prospective cohort sample is proposed to provide rigorous evidence of the effects of the full CR program. Through a stepped-wedge evaluation design, clusters (communities) cross over from control to intervention at different time points (Hussey & Hughes 2007; Brown & Lilford 2006). A community is defined as an informal settlement as this is the locus of the CR intervention. Rather than clusters being randomized to control or intervention groups for the study duration, the time at which each cluster crosses over from control to intervention is randomized (Hussey & Hughes 2007). A 2006 systematic review of published studies using stepped-wedge designs found that they were most commonly used in HIV treatment and prevention programs in developing countries (Hughes et al. 2003; Brown & Lilford 2006). The stepped-wedge evaluation design has been shown to be particularly useful for testing community-level interventions previously shown to be effective at the individual level (Hussey & Hughes 2007).

The stepped-wedge evaluation will be implemented in a subset of communities within the broader CR program implementation. In this context, the evaluation will not impede the general rollout of the CR program in non-evaluation areas. The proposed stepped-wedge design addresses several important challenges to constructing a control/comparison group in a widely implemented program such as CR: (1) CR program activities will necessarily have already begun in most targeted program communities before IRB approval is received for the evaluation, so that baseline data collection would not be possible in all CR communities without limiting the CR program; (2) communities where the CR program has not been targeted for implementation may participate in other activities during the same time period and therefore would not be appropriate control communities; and (3) the PEPFAR communities were not selected randomly (e.g., they may have higher HIV prevalence) implying that external communities may not be ideal control groups.

An illustrative schedule of the program and evaluation within a stepped-wedge approach is provided in Table 2. As is noted, a baseline survey (BL) for the cohort will be conducted in all sites at the study initiation for a period of approximately two months. Communities within the evaluation areas will be randomized to have the CR program rollout (R) in three steps at eight month intervals (Group A, Group B, and Group C), with continual implementation (I) after roll-out through the end of the program. The choice of three steps and eight month intervals for program roll-out is based on several considerations: the need to maximize the number of roll-outs (steps) in the evaluation period; the expected period of saturation of the intervention: and the expected period of program effects.^^[[10]](#footnote-11)^^ After each eight month program roll-out period, follow-up surveys (Round 2, Round 3, and Round 4) will be conducted among all study participants.

**Table 2. Illustrative schedule of program rollout and survey (32 months total)**

| **Beginning of period** | | **Aug 2016** | **Oct**  **2016** | **June 2017** | **Aug 2017** | **May 2018** | **June 2018** | **Feb 2019** |
| --- | --- | --- | --- | --- | --- | --- | --- | --- |
| Length of period (months) | | 2 | 8 | 2 | 8 | 2 | 8 | 2 |
| **Group A**  *(6 clusters)* | Survey | BL |  | R2 |  | R2 |  | R4 |
|  | Program rollout/ implementation |  | R | I | I | I | I | I |
| **Group B**  *(6 clusters)* | Survey | BL |  | R2 |  | R3 |  | R4 |
|  | Program rollout/ implementation |  |  |  | R | I | I | I |
| **Group C**  *(6 clusters)* | Survey | BL |  | R2 |  | R3 |  | R4 |
|  | Program rollout/ implementation |  |  |  |  |  | R | I |

**Notes**: In each time period, we assume two months for data collection followed by eight months for program implementation. “BL, R1, R2, R3, R4” indicates data collection; “R” indicates rapid program rollout after the respective survey has been completed; “I” indicates ongoing program implementation in the specified groups during the indicated time periods. Blank cells in the “program rollout/implementation” rows indicate that those communities will act as comparison groups during those periods.

There are several key requirements of this evaluation approach, which have important implications for implementation of the CR program:

1. *Randomized rollout of CR activities in evaluation communities*: CR activities will be rolled out randomly (at eight month intervals) within a pre-determined subset of CR communities. SOAR will work with CCI to randomize the schedule of rollout, and CCI will not initiate any program activities before rollout is scheduled for the community.
2. *Rapid rollout and saturation of all CR activities once program commences in each area*: The full package of CR activities will begin quickly throughout each community when that community’s implementation period begins. Also, the full package of CR activities should saturate each community quickly after the program commences in each cluster.
3. *Avoid contamination across clusters*: Clusters will be selected as to avoid contamination across clusters. Geographically separate clusters will be identified and the evaluation team will work with CCI to assure that the program does not cross-over into areas that are not yet scheduled for the intervention.

***Identification of study areas and eligible participants***

USAID and CCI have identified priority wards for the CR program within eThekwini and Ugu sub-districts in KwaZulu-Natal province, based on the prevalence of HIV in the area and the need for HIV prevention programming.^[[11]](#footnote-12)^ Within the identified wards, informal settlements were identified for targeting by the CR program. Depending on size, the informal settlements were further sub-divided into smaller clusters for the impact evaluation. A minimum number of households and clear demarcations (roads, highways, paths) were used as requirements for the area to by identified as a sampling cluster for the evaluation and subsequently stratified by high and low density areas. From the full list of approximately 80 informal settlements or sub-clusters, 18 were randomly selected proportional to size for the impact evaluation. After selection, clusters were than randomly ordered to receive the intervention at either the first, second, or third step as noted above in Table 1.

We propose to follow a cohort of 1,500 men and women living within each selected study cluster. Interviews will be conducted at baseline and three follow-up rounds (R2–R4). The Community Responses program as a whole aims to reach young men (aged 15–35), and young women (aged 15–24). The evaluation will be limited to men aged 18–35 and women aged 18–24. This is due to several reasons, including that: (1) the highest HIV incidence rates are found in this older age group, (2) the CR program intends to reach the younger group (aged 15–18) mainly through school-based programming, while this evaluation is particularly focusing on the effects of the community based work (including Stepping Stones, which is targeting people 20 and older), and (3) we expect that it would be quite difficult to recruit youth under 18 via the planned household-based sampling, as in-school youth would not often be found at home, and out of school 15–17 year old males are often be difficult to locate during daytime hours, when it is safer to conduct the surveys.

Eligible men and women will be sampled from households within the informal settlement. Households will be identified and sampled through the following means. All structures in the informal settlement will be manually numbered using Google Earth images and Google Earth GPS coordinates (longitude and latitude) will be assigned to the structure.^[[12]](#footnote-13)^ The structure listing will then be randomly ordered and interviewers will proceed through the list of numbered structures in the informal settlement in the order specified. A numbered map, GPS coordinates, landmarks, and distance measurements will be used to guide interviewers on the ground. If a structure is not a household it will be noted and the interviewer will proceed to the next structure on the list. A Kish grid will be used to select a household if there is more than one per structure.

One person in the eligible age group will be selected for participation per sampled household. Study interviewers wearing MatCH Research Unit identified T-shirts will approach the household and ask to speak to an adult/head of household. The interviewer will introduce themselves and offer an explanation of the study and survey and give an information sheet to the adult/head of household. They will also show a letter of permission from the ward councilor or other appropriate local gatekeeper. If the adult is willing, they will first be asked if there is at least one male or female living in the household who is within the eligible age group. If there is no individual who fulfils this criteria, the interviewer will thank the householder and proceed to the next house. If there is at least one person present who meets the study age requirements, the interviewer will continue and explain that in order to sample at the household level the fieldworker will need to list all household members (identified by age and initials only) using a household sample form (women aged 18–24, men 18–35) A Kish grid will be used to sample from the eligible household members if two or more individuals in the household meet the study inclusion criteria. If the selected individual is not in the household (working, shopping, etc.) the interviewer will ask to return at a convenient time to inform the household member about the study. The interviewer will return to the house on three different days at the preferred time in attempt to find the participant. If the participant cannot be reached after the third attempt, the interviewer will consider her/him unreachable.

Once the interviewer has obtained informed consent, the baseline survey (Annex F) will be conducted. Interviews will take place in a private location within the participant’s home. Participants will be able to choose an alternative community venue or MatCH Research offices if they do not wish to be interviewed at home. The interview will last approximately 60 minutes and will be conducted by an interviewer of the same sex as the participant. For the most sensitive questions around sexual and gender-based violence, the questions will be self-administered. Self-administration entails the participant reading the questions of the screening and entering their own responses directly without interviewer involvement. For follow-up interviews, staff will use the identifying and contact information collected at baseline to contact the participant, verify his/her identity, and conduct the follow-up survey (Annex F). If the study staff are unable to reach the participant at the follow-up interview, they will make two additional attempts on subsequent visits. Any participants who cannot be located for the follow-up interview will be noted as lost to follow-up.

Participants in the evaluation who have completed a survey may also be selected to receive a follow-up visit by CR program staff to provide more information about the CR intervention and invitation to events and/or programs that they may be interested in participating, e.g., Stepping Stones. The purpose of the outreach to survey participants is to assure sufficient exposure of study participants to the CR program and to provide a useful variable for the statistical modeling of impact (see section: Statistical analysis plan).

Specific eligibility criteria for inclusion in the evaluation are as follows:

- Between the ages of 18 and 24 (women) and 18 and 35 (men)
- Living in selected communities
- Can read in English or the local language
- Willing and able to give informed consent
- Willing to participate in three additional interviews at eight-month intervals
- Willing to provide research study staff with an identity number, address, phone number while participating in the study, and a fingerprint scan
- Agrees to participate in the study for the duration of up to three years; do not reasonably foresee moving out the study area within that time

***Primary outcomes and indicators***

Although a wide range of indicators will be measured and evaluated throughout the study period, a smaller representative set will serve as keystones for measuring program. These indicators are representative of the targeted outcomes sought by the CR program, including an increase us of HIV prevention and treatment services, reduction in sexual risk behaviors, reduction in the experience and perpetration of SGBV, and decreased support of harmful gender norms.

| **Outcome Domain** | **Indicator** |
| --- | --- |
| **Accessing HIV services** | % of participants who have obtained the results of an HIV test within the previous six months |
| **Accessing HIV services** | % of HIV-positive participants who have accessed HIV care and treatment services within the previous six months |
| **Sexual risk behaviors** | % of participants reporting using a condom at last sex |
| **Sexual risk behaviors** | % of participants reporting consistent condom use with a partner of unknown HIV status in the last 30 days |
| **SGBV** | % of participants reporting perpetrating or experiencing physical violence within the previous six months |
| **SGBV** | % of participants reporting perpetrating or experiencing sexual violence within the previous six months |
| **Gender norms** | % of participants who hold positive norms regarding gender based violence (from the GEM Scale) |
| **Gender norms** | % of participants who hold equitable norms regarding the roles of women and men (from the GEM Scale) |

**Power and sample size calculations**

To determine the required sample size of participants for the cohort, a Stata 13.0 sample size routine for stepped-wedge cluster randomized trials was used (Hemming and Girling 2014). The parameters specified for the sample size estimation include a study design with three implementation steps (of eight months in length), four total participant observations (baseline and one after each intervention step), a power criterion of 0.80, alpha coefficient of 0.05, and intra-cluster correlation of 0.05. A minimum 10% percentage point effect size (change due to intervention) was specified for the primary outcome indicators. As estimates of baseline prevalence for these indicators for the population of informal settlements by age is not readily available, the most conservative estimate of baseline prevalence (at 45%) was used. Sample size estimates were stratified by sex, such that the study is powered to draw inferences about impact separately for males and females; men and women would be sampled from different households. The minimal sample size required at the end of the study is approximately 1,260 individuals (630 men, 630 women), distributed across 18 clusters with 35 men and women in each clusters, 6 of which cross over from control to intervention at each of the three implementation steps. Assuming 15% loss to follow up, an estimated baseline sample size of 1,500 individuals (750 men, 750 women) has been specified.

**Statistical analysis plan**

The primary statistical comparison in a stepped-wedge design is between observations that have been exposed to the intervention and those that have not been exposed. In a stepped-wedge design cases will have periods of control (unexposed) and period of intervention (exposed). The first step in the analysis will be to evaluate whether the characteristics of the sampling clusters vary significantly by their original randomized implementation steps, i.e., the predetermined period of cross-over from control to intervention (Hemming et al. 2010). This analysis is conducted to assure that the original randomization did not produce early cross-over clusters that are inherently different with than later cross-over clusters. To assess balance in the clusters, analysis of community level and participant level indicators will be conducted across each of the randomized steps (Group A, Group B, and Group C from Table 2) using relatively simple statistical methods for assessing differences in grouped data, e.g., chi-square tests and t-tests.

The primary statistical approach to assessing the impact of the program will be an intent-to-treat (ITT) analysis where participants are analyzed according to their randomized period of exposure rather than whether they actually participated in the intervention at the time of implementation. While clusters are randomized to receive the CR program at a certain time, not all study participants will have actually been exposed the program when they were assigned to receive it, either because of a failure to saturate the program area or because individuals chose not to participate. The ITT analysis avoids such potential selection biases by using the exogenous random assignment of exposure as the indicator of impact. To estimate the impact within an ITT framework, generalized estimating equations (GEE) will be used that include random effects parameters for the cluster and for participants; the former to account for correlations of individuals with clusters and the latter to account for the repeated observation of participants in the cohort. Additional variables included in the regression will be calendar time, the group or period to which participants were randomized, and covariates that may play a role in the outcomes of interest (Heming et al. 2015; Hussey and Hughes 2007).

While the primary analysis and impact assessment will rely on an ITT approach, it will nonetheless be interesting to evaluate whether actual participation in the CR program predicts outcomes differentially if participation in the intervention is not 100%. It is important, however, to recognize the statistical estimation problems that result from selection into the program based on factors that can be/are measured and/or by unobservable factors. The central problem is that factors affect both participation in the program and outcomes and behaviors of interest leading to biased estimates of program impact if selection is not considered. To address these limitations, multiple estimation approaches will be explored. The first will be an instrumental variables regression, in which a model of program participation will be estimated using observed covariates and known exogenous variables, such as the original randomization period, and whether the participant was randomly chosen to receive program promotional material and outreach. A second approach will use fixed effects models that effectively control for the all unobserved constant influences from individual, family, and community characteristics.

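### Balance of participant-level indicators across rollout groups is to be checked with chi-square and t-tests, with no allowance for clustering, so a sound randomisation could be reported as imbalanced

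*Protocol*

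**What the plan says.** The Protocol, *Statistical analysis plan*, opens the analysis with a check of balance between the rollout groups. The aim is to "evaluate whether the characteristics of the sampling clusters vary significantly by their original randomized implementation steps". The reason given is: "This analysis is conducted to assure that the original randomization did not produce early cross-over clusters that are inherently different".

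The check covers two levels of data: "analysis of community level and participant level indicators will be conducted across each of the randomized steps (Group A, Group B, and Group C from" the rollout table). It is to be done "using relatively simple statistical methods for assessing differences in grouped data, e.g., chi-square tests and t-tests". No cluster-adjusted method is named for this step, and nothing is said about what follows if a difference is significant.

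Clustering is recognised elsewhere. The *Impact evaluation* section randomises the crossover time of whole clusters. *Power and sample size calculations* uses "a power criterion of 0.80, alpha coefficient of 0.05, and intra-cluster correlation of 0.05". The paragraph after the balance check includes a cluster term in the outcome model.

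**The concern.** Chi-square and t-tests in their usual form treat every participant as an independent draw. Here each rollout group consists of six whole clusters, and participants within a cluster resemble each other. A participant-level comparison of groups therefore contains between-cluster variation that the test does not count as noise, and its p-values come out too small.

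What is at stake is the purpose of the step. The check is meant to give assurance about what the randomisation produced. If it signals a difference in a large share of indicators when the allocation was carried out correctly, it gives no such assurance, and a report built on it could describe a sound randomisation as imbalanced.

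**Working it through.** **Inputs (Protocol).** 18 clusters, 6 per rollout group; baseline sample 1,500 (750 per sex); ICC 0.05; alpha 0.05, taken as two-sided; baseline prevalence 45%; 15% loss to follow-up. Equal cluster sizes are assumed.

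**The plan's own figures first.** The Protocol states no error rate for the balance tests, so its sample size is the figure to reproduce. A Hussey-Hughes calculation (3 steps, 4 measurement times, 18 clusters, ICC 0.05, 45% against 55%) gives power 0.806 at 35 per sex per cluster, and 35 is the smallest number that reaches 0.80. Then 18 × 35 = 630 per sex and 1,260 in total. Allowing for loss, 1,260 / 0.85 gives 1,483, against 1,500 stated. The inputs are therefore read as the Protocol intends.

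**Cluster size at baseline.**
- Sexes pooled: 1,500 / 18 = 83.3.
- One sex: 750 / 18 = 41.7.

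**Design effect.** DE = 1 + (m − 1) × ICC.
- Pooled: 1 + 82.3 × 0.05 = 5.12.
- One sex: 1 + 40.7 × 0.05 = 3.03.

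**True rejection rate at nominal 5% when allocation is correct.** The naive statistic is inflated by about DE.
- Three-group chi-square (2 df): P(chi-square > 5.991 / DE) = exp(−5.991 / (2 × DE)). Pooled: exp(−5.991 / 10.23) = 0.557. One sex: exp(−5.991 / 6.07) = 0.372.
- One pairwise t-test (large sample): 2 × Φ(−1.96 / √DE). Pooled: 0.386. One sex: 0.260.

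| Sample | ICC | DE | Three-group chi-square | One pairwise test |
|---|---|---|---|---|
| Pooled, 83.3 per cluster | 0.05 | 5.12 | 55.7% | 38.6% |
| One sex, 41.7 per cluster | 0.05 | 3.03 | 37.2% | 26.0% |
| Pooled | 0.01 | 1.82 | 19.3% | 14.7% |
| One sex | 0.01 | 1.41 | 11.9% | 9.8% |
| Pooled | 0.10 | 9.23 | 72.3% | 51.9% |
| One sex | 0.10 | 5.07 | 55.4% | 38.4% |

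All rates are per indicator.

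**Check by simulation.** Beta-binomial data were generated with 6 clusters in each of 3 groups, prevalence 45%, ICC 0.05 and 40,000 replicates.
- Three-group chi-square: 55.8% pooled (83 per cluster), 37.7% for one sex (42 per cluster).
- One pairwise test: 39.2% and 27.2%.
- At least one of the three pairwise tests significant: 66.7% and 51.3%.
- Chi-square at 10% prevalence, pooled: 55.5%, so the result does not depend on the 45%.

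**After the correction.** In the same simulation, one-way ANOVA on the 18 cluster proportions rejects 5.0% (pooled) and 5.2% (one sex) of the time.

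**The case against.** **The methods are only examples, and detail may sit in a separate SAP.** This stands in part. The wording leaves other methods open, so a cluster-adjusted test is not excluded. But the Protocol goes beyond leaving the method for later. It names two tests, calls them simple, and applies them to participant-level data from randomised clusters. In their usual form those tests give wrong p-values here.

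**Community-level indicators are tested too.** This stands. Tests on 18 cluster values treat the randomised unit as the unit of analysis and do not have the fault. The point covers the participant-level part of the check only.

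**The largest figure needs conditions.** This stands. The 56% is for one indicator, three groups, sexes pooled and ICC 0.05. The sample size was set separately by sex, and within one sex the figure is 37%. The ICC is a planning value for the primary outcomes; other characteristics may have a lower or higher one.

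**The clusters can be seen as fixed.** On this view, a participant-level test detects real differences between the clusters as allocated, and a rejection is not a false positive. This does not rescue the tests. The stated purpose is to judge what the randomisation of clusters produced, and the yardstick for that is how far groups of six randomly allocated clusters differ by chance. A participant-level test leaves that variation out.

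**A reader might infer that the check drives covariate choice and so biases the primary analysis.** The Protocol does not support this. It ties no action to a significant imbalance and describes the model covariates as factors that may bear on the outcomes.

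**Conclusion.** The concern holds for participant-level indicators and is minor. At the Protocol's own ICC of 0.05 and nominal 5%, a naive three-group chi-square would reject, per indicator and under correct randomisation, about 56% of the time with sexes pooled and 37% within one sex. A single pairwise t-test would reject 39% and 26% of the time. At ICC 0.01 the chi-square rates are 19–20% and 12%, still well above nominal.

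The figures assume equal cluster sizes, simple random allocation of clusters to the three groups, and tests with no cluster adjustment. Indicators asked only of a subgroup, such as HIV-positive participants, would be less inflated because fewer people per cluster contribute.

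The effect estimate, the error rate of the primary model and the sample size are not affected, and it would go too far to say that the whole balance check is invalid. What fails is the assurance the participant-level part is meant to give.

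**What to change.** Reword the balance step in *Statistical analysis plan* as follows.

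1. For participant-level indicators, describe balance with cluster-level summaries by rollout group, such as the mean and spread of the six cluster proportions or means in each group.
2. If a test is wanted, apply it to the 18 cluster means (one-way ANOVA or permutation of the allocation), or use a cluster-adjusted test. Do not report participant-level p-values that ignore the cluster.
3. State that the result of the check does not select covariates for the primary model.

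The checks on community-level values can stay. The cost is analysis wording only: no change to data collection, sample size or schedule.
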